### Sample and Randomization

Calculations were based on published evidence suggesting that approximately 90% of patients in the control group would remain constipated at 3 months. We hypothesized that this proportion would decrease to 40% in the intervention groups (BI and BIM), corresponding to a 50% absolute difference. To detect this difference with 80% power and a 2-sided significance level of 5%, while allowing for a 10% dropout rate, 15 participants per group are required. With 3 groups, the total sample size will therefore be 45 participants in total. Recruitment will take place across the 2 participating centers (Anoia and Bages), with approximately 7 to 8 participants per group expected to be recruited at each center.

The sample will be selected (1) by means of a medical history review by nursing or medical personnel; if the health professional considers that the patient meets the criteria, they will refer the patient to the research physiotherapist; and (2) indirectly, by putting up posters in *casals cívics* (civic facilities) and pharmacies in the city. Anyone learning about the study this way can make an appointment with their health professional of reference (ie, nursing or medical staff) and discuss their interest in participating in the study. If the health care professional confirms that the patient meets the criteria, they will refer the patient to the research physiotherapist.

The randomization and allocation of patients will be performed by simple randomization using the specialized software RStudio (version 4.2.1; R Foundation for Statistical Computing). The distribution is expected to be homogeneous between groups. Randomization will be conducted by an independent researcher, and allocation will be concealed using sequentially numbered, opaque, sealed envelopes prepared in advance. This procedure ensures allocation concealment and minimizes selection bias.

The chosen sample size is based on feasibility and resource availability and is sufficient to detect large effect sizes. This study aims to assess the feasibility and potential impact of the intervention and to provide effect size estimates to guide future large-scale trials.

The research physiotherapist will inform the participants of the whole process and ask for informed consent, so that they can be randomized into the 3 study groups and their data can be included in the study database for later analysis. Participants will be informed that if the expected results are obtained, they will be offered the same treatment as the intervention group that obtained the best results.

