### Design: Randomized Controlled Trial

This will be a randomized controlled trial with 3 groups: a control group, a behavioral intervention (BI) group, and a behavioral intervention and massage (BIM) group. The same number of people will be randomly distributed in each group with a 1:1:1 allocation ratio, so that the 3 groups are homogeneous for age, sex, and constipation characteristics. Data collection will be between 2024 and 2026.

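### The plan states equal, homogeneous groups, but the simple randomisation it names ensures neither; the description needs reconciling, and the continuous secondary analysis should adjust for baseline and centre

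*Protocol article*

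**What the plan says.** Four places in the protocol article bear on allocation.

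- **Design: Randomized Controlled Trial**: "The same number of people will be randomly distributed in each group with a 1:1:1 allocation ratio, so that the 3 groups are homogeneous". The sentence goes on to name age, sex and constipation characteristics.
- **Abstract, Methods**: 45 participants at 1:1:1, 15 per group overall, and roughly 22 to 23 per centre.
- **Sample and Randomization, on numbers**: "while allowing for a 10% dropout rate, 15 participants per group are required", which makes 45 over the three arms; and two centres, "with approximately 7 to 8 participants per group expected to be recruited at each center".
- **Sample and Randomization, on method**: "The randomization and allocation of patients will be performed by simple randomization using the specialized software RStudio", followed by "The distribution is expected to be homogeneous between groups". An independent researcher runs the process, and concealment is by numbered sealed envelopes made up beforehand. No blocking, stratification or minimisation is mentioned.

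The Statistical Analysis section gives a chi-square test and relative risks for the main binary variable. For the continuous secondary variable it gives ANOVA or Kruskal-Wallis, with t or Mann-Whitney tests for pairs. Centre does not appear there. Chi-square tests are also planned to relate the main variable to sociodemographic variables; these describe associations and do not adjust the treatment comparison.

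**The concern.** The Design section presents equal group sizes and homogeneity as consequences of the allocation. The method named three sections later produces neither by construction. Simple randomisation lets arm sizes vary freely, takes no account of centre, and balances covariates only on average.

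With 45 people in three arms, that variation is large relative to the arms. The article itself treats the factors at issue as relevant: the Introduction says constipation varies with sex, age and activity, and Strengths and Limitations presents the two centres as an urban and a rural setting. At stake are an accurate account of the allocation in the CONSORT report that the article promises, and some precision in a small trial.

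**Working it through.** **Inputs.** Total 45, 15 per group, 90% against 40% still constipated at 3 months, 80% power, two-sided 5%, 10% dropout (Sample and Randomization); 22 and 23 per centre (Abstract).

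**1. The plan's own sample size.** For two proportions with pooled variance and no continuity correction, the mean proportion is 0.65 and

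n = [1.960·√(2·0.65·0.35) + 0.842·√(0.9·0.1 + 0.4·0.6)]² / 0.5² = (1.322 + 0.483)² / 0.25 ≈ 13.0.

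Dividing by 0.9 for dropout gives about 14.5, which rounds up to the stated 15. (Rounding up to 14 before allowing for dropout gives 16.) The figure is reproduced and is not in dispute.

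**2. Arm sizes if the 45 allocations were independent draws at 1/3 each.**

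- P(15/15/15) = 45! / (15!)³ / 3⁴⁵ = 0.0181.
- P(14/15/16 in a given order) = 0.0181 × 15/16 = 0.0170. There are six orders, so P(all arms 14 to 16) = 0.0181 + 6 × 0.0170 = 0.120.
- Full enumeration: P(smallest arm ≤ 10) = 0.221; P(smallest arm ≤ 12) = 0.611; P(largest minus smallest ≥ 5) = 0.707.
- SD of one arm size = √(45 · 1/3 · 2/3) = 3.2; 95% range 9 to 21.

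**3. Centre by arm.** All three arms fall at 7 or 8 with probability 0.105 in a centre of 22 and 0.101 in a centre of 23. For both centres together this is 0.105 × 0.101 ≈ 0.011. In simulation (400,000 draws) some centre-by-arm cell has 4 or fewer people in 45% of draws.

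**4. Homogeneity.** The chance that two arms differ by at least 25 percentage points was simulated under independent draws and under a shuffled list of exactly 15/15/15. The trial's sex mix is not given; 30 women of 45 is an assumption taken from the 2:1 ratio in the Introduction, with 23 to 36 as the range.

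| Characteristic | Independent draws | Shuffled 15/15/15 |
|---|---|---|
| Share from one centre | 39% | 42% |
| Share of women, 30 of 45 | 35% | 36% |
| Share of women, 23 of 45 | 38% | 42% |
| Share of women, 36 of 45 | 23% | 25% |

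Fixing the arm sizes therefore does not rescue the homogeneity claim. It also leaves all six centre-by-arm cells at 7 or 8 in only 19% of draws. Blocks of three within each centre would have given 7/7/8 and 7/8/8, but even they would not balance age, sex or severity.

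**5. Power for one intervention arm against control.** With 15 × 0.9 = 13.5 evaluable per arm:

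z = (√13.5 · 0.5 − 1.322) / 0.574 = 0.897, power 81.5%.

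Over random arm sizes with the same dropout (50,000 draws), mean power is 79.8%, the 5th percentile is about 70%, and 46% of draws fall below 80%. The average loss is 81.5 − 79.8 = 1.7 points.

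**6. Control recoveries.** At 90% still constipated, 15 × 0.10 = 1.5 recoveries are expected, and the chance of none is 0.9¹⁵ = 21%. This limits what a covariate-adjusted logistic model could do for the binary outcome.

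**The case against.** The strongest reply is that the figures in step 2 depend on one reading. Envelopes made up beforehand for a fixed total of 45, together with the repeated 15 per group, fit a shuffled 15/15/15 list that was called simple only because it was unstratified. The article cannot settle this. The point stands: under that reading the arm sizes are exact and step 2 does not apply. But the method is then misnamed, and step 4 shows that homogeneity is still not ensured.

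Three stronger readings are tempting and are not supported.

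- **That the per-centre numbers are broken promises.** They are worded as approximate and expected. The statement that the distribution is expected to be homogeneous is likewise true on average. The firm conflict is with the Design section only.
- **That the comparison is biased or the planned tests invalid.** Simple randomisation is unbiased, and the error rate of an unadjusted test already allows for chance imbalance. An unadjusted test is also a natural match to unstratified allocation.
- **That adjustment has been overlooked.** Any separate analysis plan is not shown, and covariate choice is often left to it. Adjustment is recommended here only because the article itself fixes unadjusted tests where a baseline measurement is available.

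It is also fair to say that replacing the primary binary comparison with an adjusted regression would be a poor trade: few control recoveries are expected, and an ordinary logistic fit could separate.

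**Conclusion.** The Design and the Sample and Randomization sections contradict each other on a stated design property. Simple randomisation could yield 15/15/15 but does not ensure it: the chance is 1.8% if the draws were independent. The homogeneity claim is unsupported whether the draws were independent or the list was fixed at 15/15/15.

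The consequence is moderate. Validity is intact, and the average power loss is about 2 points, with a 5th percentile near 70%. What remains is chance imbalance and lost precision, plus an inaccurate account of the method. The arm-size and power figures assume independent draws with equal probability; the power figures also take the plan's 90% and 40% rates and 10% dropout at face value. The sex figures rest on an assumed mix.

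**What to change.** Enrolment ended in August 2025 and data collection runs to April 2026, so the allocation cannot change but its description and the analysis can.

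1. **State how the envelope list was generated**, and make the Abstract, Design, and Sample and Randomization sections agree with it.
   - If it was simple: withdraw the claim of equal numbers and the claim that homogeneity follows, and report actual arm sizes by centre.
   - If it was a fixed 15/15/15 or blocked list: correct the label of simple randomisation, and still withdraw the claim that homogeneity for age, sex and constipation follows.
2. **Before unblinding, replace the unadjusted ANOVA and t tests for the continuous secondary outcome with an ANCOVA** on its T0 value and centre. The outcome is taken here to be CVE-20, since quality of life is the secondary objective; Table 1 collects it at T0.
3. **Keep the unadjusted comparison as primary for the binary outcome.** Add a centre-adjusted risk difference or relative risk, for example Mantel-Haenszel, as a sensitivity analysis.

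The cost is some rewording, a dated amendment to the analysis, and two terms in one model. No new data or participants are needed.

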### Intervention

#### BI Group

The behavioral education sessions are structured into two 60-minute workshops delivered in a progressive format. Session 1 focuses on understanding the physiology of defecation, the Rome IV diagnostic criteria, and bowel habits. Session 2 addresses lifestyle-related components, including dietary fiber and hydration guidelines, physical activity recommendations, stress management, optimal defecation posture, and the rational use of laxatives. The sessions are delivered by a multidisciplinary team (nurse, physician, physiotherapist, nutritionist, and psychologist) using multimedia presentations and printed handouts. Participants are encouraged to set personal bowel health goals. Questions and doubts raised during the first session will be discussed and resolved in the second session, ensuring continuity of learning and participant engagement.

The Bristol scale, Rome IV criteria, CVE-20 quality of life questionnaire, and International Physical Activity Questionnaire (IPAQ) [11,29-31] will be explained, and a calendar will be given to the patients to mark when they take any laxatives. Once the information sessions are complete, follow-ups will be scheduled 3 and 6 months later.

#### BIM Group

The BIM group will receive the same intervention as the BI group, and the group will also participate in two 30-minute sessions with the physiotherapist to learn how to perform abdominal massage. In these sessions, the technique will be explained and an explanatory leaflet will be given to the participants so that they can do the massage independently at home.

The abdominal massage protocol follows a standardized clockwise technique that mirrors the path of the colon. The massage begins in the right lower quadrant (ascending colon), progresses to the upper abdomen (transverse colon), and concludes in the left lower quadrant (descending colon). Techniques include gentle effleurage, deep circular kneading, and vibration movements, applied in a slow, consistent rhythm. Each session lasts approximately 30 minutes. Participants are instructed to perform the massage once daily, preferably 20 to 30 minutes after a main meal, in a supine position with knees slightly flexed. The physiotherapist demonstrates the technique and provides a printed visual guide for home practice. The therapist will verify that participants have correctly learned the abdominal massage technique and are able to perform it independently.

To support adherence to the abdominal massage protocol, participants will be provided with a daily self-recording calendar to note each time they perform the massage at home. This calendar will be reviewed at follow-up visits. In addition, weekly SMS reminders will be sent to participants in the BIM group, encouraging them to maintain the daily routine and reinforcing key points of the technique.

Once these sessions are finished, follow-up sessions will be scheduled at 3 and 6 months. Participants will complete the questionnaires again and return the calendar, with marks showing when laxatives were used and massages performed.

#### Control Group

The control group will receive the usual care in their primary care center and will be asked to complete the Bristol scale, Rome IV criteria, CVE-20 quality of life questionnaire, and IPAQ [11,29,30] at the beginning of the study and after 3, 6, and 12 months. They will also be given the calendar to mark when they take laxatives. This calendar will be collected after 3 months.

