The primary objective of this study is to evaluate the effectiveness of a structured rehabilitation program based on behavioral reeducation and abdominal massage therapy in reducing the prevalence of chronic constipation and the use of laxatives at 3, 6, and 12 months after the intervention. The secondary objectives are to assess changes in quality of life among participants and to evaluate whether the observed effects are sustained over time.

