#### Access to Usual Care

All participants in the study, including those in the BI and BIM groups, will continue to have access to usual care throughout the study period. Usual care refers to the standard clinical management offered by primary care physicians and nurses, which may include dietary advice, physical activity counseling, laxative prescriptions, or follow-up visits, depending on individual needs and clinical judgment. No restrictions are placed on access to routine health care.

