### Variables

We will evaluate a set of indicators on constipation and other patient characteristics, as shown in Table 1. Outcomes will be assessed individually and at 5 different time points: before starting the intervention, on the same day of the intervention, 3 months after the intervention, 6 months after the intervention, and 12 months after the intervention. Data will be collected through standardized questionnaires to be completed independently by the participants.

**Table 1. T1:** Study variables.

Study area and instrument		Measurement time point
Constipation		
	Rome IV criteria—degree of constipation	Tpre^a^, T0^b^, T3^c^, T6^d^, T12^e^
	Bristol Stool Form Scale—stool type	T0, T3, T6, T12
Quality of life		
	CVE-20 questionnaire	T0, T3, T6, T12
Use of laxatives		
	Self-recorded calendar of laxative intake	T3, T6, T12
Patient characteristics		
	ECAP^f^—sex, age, previous conditions	Tpre
	IPAQ^g^—physical activity level	T0, T3, T6, T12
Habit change intention		
	Dichotomous question	T0

a Tpre: before the intervention.

b T0: start of the intervention.

c T3: 3 months after the intervention.

d T6: 6 months after the intervention.

e T12: 12 months after the intervention.

f ECAP: Electronic Primary Care Clinical Workstation.

g IPAQ: International Questionnaire of Physical Activity.

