## Discussion

### Principal Anticipated Findings

We anticipate that the structured rehabilitation program combining behavioral reeducation and abdominal massage will lead to a reduction in chronic constipation symptoms and laxative use at 3 and 6 months after the intervention. We also expect improvements in quality of life, particularly among participants receiving both behavioral education and massage therapy. Furthermore, we expect that both intervention groups will show improvements compared to the control group, but that the BIM group will experience greater improvements.

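### Laxative use is in the primary objective at 3, 6 and 12 months, but the control calendar is described as collected at 3 months, against Table 1, and no arm has a baseline laxative measure

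*Protocol article*

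**What the plan says.** The objectives paragraph that closes the Introduction sets the primary aim as "reducing the prevalence of chronic constipation and the use of laxatives at 3, 6, and 12 months after the intervention". Principal Anticipated Findings repeats the expectation for the first two follow-ups: a "reduction in chronic constipation symptoms and laxative use at 3 and 6 months after the intervention".

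The measurement of laxative use is described in several places:

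- **Control Group.** The questionnaires are completed "at the beginning of the study and after 3, 6, and 12 months". The laxative calendar is dealt with separately: "This calendar will be collected after 3 months". No later collection is mentioned.
- **BIM Group.** After naming follow-up sessions at 3 and 6 months, the text has participants "return the calendar, with marks showing when laxatives were used and massages performed".
- **BI Group.** A calendar is handed out and follow-ups are set at 3 and 6 months. Return of the calendar is not spelled out.
- **Variables, Table 1.** The row "Self-recorded calendar of laxative intake" carries T3, T6 and T12, with no arm restriction and no Tpre or T0 entry.
- **Abstract, Methods.** Follow-up at 3 and 6 months uses the calendar, again for participants in general. The baseline instruments named are Rome IV, Bristol, CVE-20 and IPAQ.

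The clinical record (ECAP) is listed in Table 1 at Tpre for sex, age and previous conditions, not for laxatives. Under Access to Usual Care, which includes laxative prescription, "No restrictions are placed on access to routine health care".

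**The concern.** Laxative use is half of the stated primary objective, and two things in the plan work against answering it.

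First, the control text and Table 1 give different collection schedules. The control paragraph gives the questionnaires three follow-up points and the calendar one, so staff could reasonably take it to mean a single collection. They would then hold no control laxative data after month 3, and a daily diary that was never kept or collected cannot be reliably rebuilt later.

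Second, the objective speaks of a reduction, but no starting value is listed for any arm. Laxatives are open to everyone, and their rational use is taught in the BI and BIM sessions, so use may well move differently by arm. Without a baseline, the analyst can compare use between arms after the intervention, but cannot estimate change, adjust for entry use, or see whether the arms started alike.

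**Working it through.** **1. Calendar schedule, place by place**

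| Time point | Objective (Introduction) | Table 1 | Abstract | Control Group text | BIM Group text |
|---|---|---|---|---|---|
| Tpre / T0 | – | no | no | no | no |
| 3 months | yes | yes | yes | yes | yes |
| 6 months | yes | yes | yes | no collection stated | yes |
| 12 months | yes | yes | not mentioned | no collection stated | no follow-up stated |

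All sources agree only at 3 months. At 6 months the control text departs from Table 1 and the abstract. At 12 months it departs from Table 1 and the objective, and the BI and BIM sections state no 12-month follow-up either. If Table 1 governs, control calendars exist at T6 and T12. If the control text governs, they do not, and a randomised comparison of laxative use is available at 3 months only.

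**2. The plan's own figure**

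The protocol gives no figure for laxative use. Its 15 per group (Sample and Randomization) rests on constipation at 3 months: 90% against 40%, 80% power, two-sided 5%, 10% dropout.

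- Arcsine formula: h = 2·asin(√0.9) − 2·asin(√0.4) = 1.129. Then n = 2(1.960 + 0.842)²/h² = 12.3, so 13, and 13/0.9 = 14.4, so 15.
- Pooled normal formula, no continuity correction: 14, and 14/0.9 = 15.6, so 16.

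The stated 15 is reproduced. It says nothing about laxative use and is needed here only as the arm size.

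**3. How often the arms would differ at entry by chance**

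Let X and Y be the numbers of laxative users at entry in two arms of 15, independent Bin(15, p). The protocol gives no p, so it is an assumption and is varied. By exact enumeration:

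P(|X − Y| ≥ 3) = 1 − P(X = Y) − 2·P(X − Y = 1) − 2·P(X − Y = 2)

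At p = 0.4: 1 − 0.1475 − 2(0.1379) − 2(0.1126) = 0.351.

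| Assumed entry use p | P(difference of at least 3 users) |
|---|---|
| 10% or 90% | 0.12 |
| 20% or 80% | 0.25 |
| 40% or 60% | 0.35 |
| 50% | 0.36 |

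Three users out of 15 is 20 percentage points. The table shows how often such an imbalance arises. It does not measure bias in the trial's test, whose error rate already allows for chance imbalance.

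**4. Is collection still possible?**

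The Progress section has enrolment ending in August 2025 and data collection running to April 2026. Six months from August 2025 is February 2026, inside that window. Twelve months is August 2026, outside it. So the 6-month calendar can be secured for later enrolees, whereas the 12-month one depends on whether that visit is kept.

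**The case against.** The strongest reply is that the control sentence does not say the calendar is collected at 3 months *only*. Table 1 and the abstract schedule it later without excluding controls, and the arm sections are plainly shorthand: the BI section does not mention return of the calendar at all. On that view this is a drafting slip. That stands to this extent: the documents contradict each other and do not settle that control data will be missing. It does not remove the need to act, because site staff may follow the arm-specific text.

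The second reply is that randomisation makes a post-intervention comparison valid without any baseline. That stands in full. The loss is in precision, in checking balance and in estimating change.

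The third concerns Rome IV status. A reader might infer that the main comparison cannot be interpreted, because someone free of symptoms on daily laxatives would count as cured while laxative use goes unmeasured. The documents do not support this. Calendars are scheduled in all arms at 3 months, the time point behind the sample size. Textbox 1 also refers to spontaneous bowel movements and to laxatives in its wording, and the article does not describe how treated participants are scored.

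Finally, the main variable under Statistical Analysis is constipation status, so that analysis does not depend on the calendar.

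**Conclusion.** The point holds as a contradiction plus a gap. Laxative use belongs to the primary objective at three follow-up times, and the control text conflicts with Table 1 at two of them. If the control text is followed, no randomised laxative comparison exists at 6 or 12 months; if Table 1 is followed, it does.

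No baseline laxative measure is listed in any arm, so a reduction from baseline cannot be estimated from the listed data. Chance imbalance of 3 or more users between two arms of 15 has a probability of 0.12 to 0.36 over assumed entry use of 10% to 90%, and the listed data would not show it.

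Two stronger conclusions that a reader might draw are not supported: that a valid 6-month comparison is already ruled out, and that the 3-month comparison is invalid for want of a baseline.

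**What to change.** 1. **Reconcile the Control Group text with Table 1.** All arms should keep and return the same calendar at every time point for which a laxative claim is made: T3, T6, and T12 if that visit is retained. Do this while data collection is open. State calendar return in the BI section too.
2. **Where control calendars after T3 were not collected,** restrict the laxative claim to 3 months.
3. **Add baseline laxative use** from prescription records in ECAP dated before enrolment, and use it as a covariate. That ECAP holds these data in usable form is an assumption, since Table 1 lists only other items from it.
4. **If no baseline can be obtained,** word the result as a between-arm difference in post-intervention use, not as a reduction from baseline.
5. **Optional:** a supportive analysis that reads Rome IV status together with laxative use from the calendar.

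The cost is a few more calendars and one records query. Prescription records miss over-the-counter use, so the baseline would be partial. Asking participants now to recall earlier use should not be relied on to fill that gap: they are unblinded, two arms have been taught about laxatives, and recall may differ by arm.
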